### Subaim 2a

The purpose of subaim 2a is to characterize the social network structure and behaviors using process data obtained in the virtual environment. We will collect continuous process data from recording and tracking of all interactions within the virtual environment. We expect that the process data will reveal disarticulated patterns, behaviors, and utilization of networks, and show the structure of these networks as they are used by participants in obtaining information [50]. This is important, as the data will be used to identify how social processes affect behavior change [70] and leverage these networks to influence new social norms and behaviors [70]. In the unlikely event that there are technical issues during participant usage, information technology professionals who have designed and worked on LIVE for many years will be available to assist the study team.

### Sample Size Calculation

The purpose of this study is to test the feasibility and acceptability of a virtual environment and obtain preliminary estimates of potential effects on behavioral and psychosocial outcomes in the prevention of cardiovascular comorbidities in persons with HIV. This is not a definitive test of intervention efficacy. Previous research has shown that feasibility studies with a sample size of at least 10 are sufficient to address our aims [30,71]. We believe our sample size of 80 participants (40 intervention subjects and 40 waitlist control subjects) will yield interval estimates of potential intervention efficacy that will be useful for making decisions about next steps (ie, whether to perform more intervention development or launch a larger trial). Power calculations show the planned sample size will produce a 95% CI for mean differences with an expected half-width of 0.45 SD, conveying the precision of preliminary estimates of efficacy.

### Data Analysis

#### Aim 1

Directed content analysis will be used to analyze qualitative data. Directed content analysis is appropriate, as it utilizes a theoretical framework to extend knowledge of data content through a systematic process of coding and identification of categories, themes, and patterns from the interview data [72,73].

#### Measures of Methodological Rigor

Reliability will be demonstrated by providing a detailed description of the study’s purpose, participant sampling, and rationale, as well as the role of the researchers and study team involved [74] and our consistent approach (indicating dependability) to qualitative data collection in aim 1 [75]. Validity will be ensured through member checking [74] of the accuracy and credibility of our findings from the aim 1 interviews. Debriefings will be held after the interviews conclude to determine the validity of our interpretation [74].

#### Aims 2 and 2a

Data will be analyzed using Statistical Package for Social Sciences (SPSS, IBM Corp). Descriptive statistics will describe participant demographics. To determine whether the intervention is acceptable and feasible, the standard will be an acceptability rating of “good” or “very good,” good engagement, and timely completion of study activities in at least 80% of participants. If these standards are met or exceeded, we can conclude that acceptability and feasibility are sufficient for a larger trial. If they are not met, additional formative work on the intervention will be undertaken. CIs for effect sizes will indicate the potential clinical and public health significance and substantiate the need for a larger, more robust clinical trial.

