### Eligibility

In order to meet enrollment criteria, participants must (1) be a cisgender male between ages 30 and 65; (2) identify as an ethnic or racial minority; (3) have HIV; (4) identify as gay, bisexual, or queer; (5) read and understand English; (6) have access to a computer capable of downloading and running the virtual environment software; and (7) have no cognitive impairment and no medical history of serious complications, such as myocardial infarction, congestive heart failure, coronary artery bypass graft, or cerebral vascular accident. It is documented that the highest incidence of HIV is among emerging adults (ie, up to 34 years old) [46], as chronic illness is becoming diagnosed at earlier stages of life (eg, 18 to 30 years old) with the highest prevalence at age 50 years and older [47]. Our sample age range is appropriate given the changing age demographic of chronic illness and will provide a thorough overview spanning 3 generations.

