### Recruitment

To increase the feasibility of participant enrollment and data collection and to use existing resources more efficiently, we will utilize a preexisting HIV registry and employ respondent-driven sampling for aims 1 and 2. Respondent-driven sampling is an ideal approach to purposively draw participants that are similar because of their connections (eg, having HIV, identifying as a sexual-minority male, and having ethnic or racial minoritized heritage), known as homophily [48-50]. This approach is fitting as a potential preemptive when recruiting historically under-sampled communities [51,52]. To prevent enrollment shortfalls, we will also partner with community-based organizations who serve LGBTQ+ populations in the New York City area. Zoom (Zoom Video Communications, Inc) will be used as the primary method of communication for enrollment, orientation to the study, and data collection in aim 1.

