## Results

The study is part of a 5-year mentored research development award that received funding from the National Heart, Lung, and Blood Institute on September 1, 2019. The first 2 years of the award were developmental. The remaining 3 years will focus on data collection, analysis, dissemination, and an application for a large-scale follow-up grant. We have published 2 manuscripts formative to this research. The first outlined a framework for using eHealth interventions for chronic illness prevention in sexual-minority men of color [39]. The second manuscript was a scoping review assessing nonpharmacologic behavioral and lifestyle interventions to prevent CVD in persons with HIV [87]. Moreover, aim 1 data collection is 87% complete. We expect to complete all data collection for aim 1 on or before April 30, 2022. Recruitment for aim 2 will begin mid-May 2022.

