### Limitations

This study is not without limitations. First, the study is not sufficiently powered to detect intervention efficacy. We are testing the feasibility and acceptability of using a virtual environment. Because of this, generalizability is limited. However, our findings will inform any changes or refinements needed for a larger trial. Second, the use of a virtual environment for CVD prevention education may be daunting for persons who are not avid users of technology and may create a barrier to recruitment. We have tried to mitigate this by creating a frequently asked questions brochure. We will also offer orientation prior to the intervention and technical support as needed. Additionally, prior research on older adults suggests that a large proportion of middle-aged to older adults are now playing online games for entertainment and mental sharpness [92]. Third, recruitment may be slow, due to concerns about privacy and confidentiality in a study focused on CVD prevention in persons with HIV. We will reinforce that the virtual environment is an anonymous online space and that all interactions will be via a user-created avatar who uses a pseudonym.

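### The rule for proceeding to a larger trial counts only enrolled men and has no recruitment condition, so it can be met even if far fewer than the planned 80 are recruited

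*Protocol article*

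**What the plan says.** The Protocol article, Data Analysis, Aims 2 and 2a, sets a standard with three parts: an acceptability rating in the top categories, "good engagement, and timely completion of study activities in at least 80% of participants". It then states what follows from success: "If these standards are met or exceeded, we can conclude that acceptability and feasibility are sufficient for a larger trial". It also states what follows from failure: "If they are not met, additional formative work on the intervention will be undertaken". There is no branch for recruitment.

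Elsewhere the article treats enrolment as a possible difficulty. In Recruitment: "To prevent enrollment shortfalls, we will also partner with community-based organizations who serve LGBTQ+ populations in the New York City area". In Limitations, use of a virtual environment "may be daunting for persons who are not avid users of technology and may create a barrier to recruitment", and "recruitment may be slow, due to concerns about privacy and confidentiality in a study focused on CVD prevention in persons with HIV".

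Sample Size Calculation plans 80 men, 40 per group, and says the results will inform the choice between developing the intervention further and starting a bigger trial.

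**The concern.** A man can rate, use and complete the programme only after he has joined. The three measures therefore describe how enrolled men fared. They do not show whether enough men could be enrolled. The rule is nevertheless written as a sufficient condition, and its conclusion concerns a larger trial, for which the ability to recruit is essential.

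If recruitment stalled and the few men who joined were content and compliant, the rule would still say that feasibility had been shown. A larger trial could then be proposed although the pilot had run into a problem its authors had named in advance. The failure branch does not help, because it is triggered only by the same three measures and leads only to more work on the intervention.

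**Working it through.** **Inputs from the article.** Threshold: at least 80% of participants (Aims 2 and 2a). Planned enrolment: 80, split 40 and 40, with an expected 95% CI half-width of 0.45 SD for a mean difference (Sample Size Calculation). Aim 2 recruitment opens mid-May 2022, and the 5-year award was received on 1 September 2019 (Results).

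**Assumed inputs.** Enrolment totals below 80, and true success rates of 70% and 85%. The article gives neither.

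**Step 1: reproduce the article's precision figure.** Half-width = t(0.975; N − 2) × √(2/n), with n = N/2 per group. For N = 80: 0.445 SD with t on 78 degrees of freedom (0.438 with the normal value). This rounds to the stated 0.45.

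**Step 2: apply the 80% rule at smaller enrolment.** The smallest passing count is r = 0.8 × N, rounded up. The interval is the exact (Clopper-Pearson) 95% CI around r/N. The chance of passing is P(X ≥ r) with X binomial(N, p), for one criterion taken alone.

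| Men enrolled (N) | Passing count (r) | r as share of planned 80 | 95% CI around r/N | Chance of passing, p = 0.70 | Chance of passing, p = 0.85 | CI half-width for a mean difference (t) |
|---|---|---|---|---|---|---|
| 80 | 64 | 80% | 0.70 to 0.88 | 0.03 | 0.92 | 0.45 SD |
| 40 | 32 | 40% | 0.64 to 0.91 | 0.11 | 0.87 | 0.64 SD |
| 20 | 16 | 20% | 0.56 to 0.94 | 0.24 | 0.83 | 0.94 SD |

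Two results follow. First, the rule gives the same answer at 32/40 and 16/20 as at 64/80. Second, low enrolment makes a wrong pass more likely: at a true rate of 70%, the chance rises from 0.03 with 80 men to 0.11 with 40 and 0.24 with 20.

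**Step 3: look for another place where enrolment could stop the decision.** Recruitment lists an action against shortfalls, not a criterion. Timely completion is counted among participants, so it cannot stand in for accrual. Sample Size Calculation sets no minimum that must be reached; it regards even 10 or more as adequate for a feasibility study.

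**Step 4: what accrual rate would 80 men need?** This depends on assumptions. If the award ends on schedule at the end of August 2024, 27.5 months remain from mid-May 2022.

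- Last man followed for 6 months: 27.5 − 6 = 21.5 months; 80/21.5 = 3.7 per month.
- Last man followed for 12 months: 27.5 − 12 = 15.5 months; 80/15.5 = 5.2 per month.
- As above, with an assumed 6 months kept for analysis and the grant application: 15.5 − 6 = 9.5 months; 80/9.5 = 8.4 per month.

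The range is about 3.7 to 8.4 per month. The beta test that precedes the trial could shorten any of these windows.

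**The case against.** The strongest reply is that the rule concerns the intervention. The paragraph opens by asking whether the intervention is acceptable and feasible, and its failure branch is more work on the intervention. For that question, ratings, engagement and completion are the right measures. This stands as a description of the measures. It does not rescue the conclusion, which speaks of a larger trial. Narrowing that sentence would be one legitimate repair.

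A second reply is that accrual targets and screening logs usually sit in a full protocol. That is true, and their absence here is not the complaint. The article publishes a condition said to be sufficient; a recruitment condition held elsewhere would conflict with it.

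A third reply is that the 80% rule is not the only input, since effect-size intervals also inform next steps. Those intervals would widen with low enrolment, as Step 2 shows, but no width is set that would block a go decision.

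One could also take the 80% as a share of the planned 80. Then 64 successes would always be needed and recruitment would count implicitly. The article does not say so.

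Three stronger readings should be resisted:

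- A reader might infer that the authors expect recruitment to fail. They say only that it may be slow and that technology may be a barrier, and they plan mitigation.
- A reader might turn the monthly rates into a threshold. They rest on assumed follow-up and reserve time, and they measure whether this award finishes on time, not whether a larger trial could recruit.
- A reader might add that the requirement to "have access to a computer capable of downloading and running the virtual environment software" leaves only a computer-owning minority. The criterion asks for access, not ownership; nothing in the article indicates a minority; and eligibility is a separate question from the decision rule.

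**Conclusion.** The point holds in a limited form. The published rule can conclude that a larger trial is feasible on evidence that says nothing about recruitment, and it gives that answer at 32/40 or 16/20 as readily as at 64/80. That much follows directly from the wording and needs no assumption beyond reading participants as those enrolled.

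The enrolment shortfalls are illustrative, and nothing in the article suggests that half the men will be missing. The probabilities of a wrong pass rest on the assumed true rate and on one criterion taken alone; requiring all three jointly would change them. The defect does not depend on any particular accrual rate. It matters because feasibility is a stated aim of the trial and this rule decides the next step.

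**What to change.** Before aim 2 opens, add a recruitment condition to the standard in Aims 2 and 2a. For example, a go decision would also require the planned 80 men to be randomised within an accrual window that the sponsor sets in advance. Report the numbers approached, eligible and consenting alongside it. State that the 80% is a share of randomised men.

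If the recruitment condition is missed, limit the conclusion to acceptability and feasibility of the intervention among those enrolled, and rework recruitment before proposing a larger trial.

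The cost is one added criterion and a screening tally, with no extra participants or visits. The downside is that a go decision becomes somewhat harder to reach.

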#### Incomplete or Missing Data

To address the potential for incomplete or missing data while maximizing statistical power and reducing the likelihood of bias, several procedures based on differing assumptions about the random nature of the missing data will be implemented [76]. Missing values may be handled by the full information maximum likelihood method, [77] which works by finding model parameters that maximize the likelihood of each case’s observed data [78]. Inverse probability weighting [79,80] and multiple imputation [81-83] will be considered as well. These approaches to handling missing data assume that data are missing at random; that is, missing at random conditionals on values of observed variables. In addition, methods for nonignorable missing data (ie, missing not at random), such as Heckman’s selection model [77,84] and pattern-mixture models [81,85,86], will be used. Sensitivity analyses will be used to determine the degree to which results depend on untestable assumptions.

## Results

The study is part of a 5-year mentored research development award that received funding from the National Heart, Lung, and Blood Institute on September 1, 2019. The first 2 years of the award were developmental. The remaining 3 years will focus on data collection, analysis, dissemination, and an application for a large-scale follow-up grant. We have published 2 manuscripts formative to this research. The first outlined a framework for using eHealth interventions for chronic illness prevention in sexual-minority men of color [39]. The second manuscript was a scoping review assessing nonpharmacologic behavioral and lifestyle interventions to prevent CVD in persons with HIV [87]. Moreover, aim 1 data collection is 87% complete. We expect to complete all data collection for aim 1 on or before April 30, 2022. Recruitment for aim 2 will begin mid-May 2022.

## Discussion

### Principal Aims

We will conduct a waitlist randomized controlled feasibility trial of a virtual environment to provide education on CVD prevention to sexual-minority men of color with HIV who are 30 to 65 years old, which to our knowledge has not been done before. We anticipate that using an anonymous virtual environment for prevention education will have great potential to facilitate health-promoting behaviors over the course of the study and thereafter. Strategies for mitigating challenges were created and will be implemented for all aims, as described above. This study has the potential to inform strategies for chronic illness prevention using a virtual environment in underserved and stigmatized communities, which is advantageous, as technology usage as a means of information seeking and education is standard. In a 2011 survey, 83% of adults with a chronic condition reported using the internet to search for health information [88]. According to a Pew Research poll, 98% of adults 30 to 49 years old and 96% of adults 50 to 64 years old are internet users [89]. Moreover, the proportion of adults who have smartphones (and live in households with incomes less than 30 thousand dollars per year) has increased by more than half [90]. This illustrates the changing demographics and reach of technology use in older age groups and in lower socioeconomic status groups. With the evolving advances in eHealth strategies and uptake in use, virtual environments can become a leading tool for chronic illness risk reduction, as 43% of adults 50 years or older are using technology for health and 38% are using it for skill building [91].

### Limitations

This study is not without limitations. First, the study is not sufficiently powered to detect intervention efficacy. We are testing the feasibility and acceptability of using a virtual environment. Because of this, generalizability is limited. However, our findings will inform any changes or refinements needed for a larger trial. Second, the use of a virtual environment for CVD prevention education may be daunting for persons who are not avid users of technology and may create a barrier to recruitment. We have tried to mitigate this by creating a frequently asked questions brochure. We will also offer orientation prior to the intervention and technical support as needed. Additionally, prior research on older adults suggests that a large proportion of middle-aged to older adults are now playing online games for entertainment and mental sharpness [92]. Third, recruitment may be slow, due to concerns about privacy and confidentiality in a study focused on CVD prevention in persons with HIV. We will reinforce that the virtual environment is an anonymous online space and that all interactions will be via a user-created avatar who uses a pseudonym.

### Conclusion

This study will be the first online virtual environment intervention to address CVD prevention in sexual-minority men of color with HIV. We anticipate that the intervention will be beneficial for CVD prevention education and building peer social supports and will result in changes or modifications in risk behaviors for CVD over time. The ways in which the virtual environment is leveraged can potentially inform strategies on implementation of technology-based behavioral interventions in under-sampled and minoritized communities who are at risk of preventable chronic conditions.

## Appendix

Multimedia Appendix 1 Proposal peer-reviewed summary statement from the National Heart, Lung, and Blood Institute Special Emphasis Panel - K01 Career Development Programs to Promote Diversity in Health Research.

## Abbreviations

CVD: cardiovascular disease
LIVE: Learning in a Virtual Environment
